## Introduction

1

Uremic pruritus (UP) is a prevalent and distressing complication of end-stage renal disease (ESRD), affecting approximately 40–90% of patients undergoing maintenance hemodialysis (Sanchez-Alvarez et al., 2024). UP is characterized by persistent or paroxysmal severe itching, that profoundly impairs sleep quality, emotional well-being, and social functioning, thereby reducing patients’ quality of life; it is also associated with increased mortality risk (Tennankore et al., 2024). Current therapeutic options for UP include antihistamines, topical emollients, phototherapy, gabapentin or pregabalin, and opioid receptor modulators (e.g., difelikefalin, nalfurafine). These treatments have limitations in efficacy, adverse effects, or accessibility (Kljajić et al., 2026), underscoring the need for safe and effective complementary or alternative therapies.

Acupuncture, a core component of traditional Chinese medicine, has been shown to effectively alleviate UP symptoms in numerous clinical studies, including reducing pruritus severity and improving sleep and mood (Yeam et al., 2021; Zhang et al., 2023). Additionally, some research suggests that its benefits for UP in patients with ESRD are related to the regulation of peripheral immune responses, including decreasing serum levels of interleukin-2, histamine, and 5-hydroxytryptamine (Ardinata et al., 2022; Gan et al., 2023). Although our previous studies have highlighted the importance of central integration in the effects of acupuncture (Yin et al., 2023a; Yin et al., 2023b), the central mechanisms underlying its therapeutic effects on UP remain unclear. Understanding how acupuncture modulates brain activity during clinical treatment is important for optimizing therapeutic strategies. Therefore, it is necessary to explore the central mechanisms of its antipruritic effects on UP.

Functional near-infrared spectroscopy (fNIRS) offers advantages for investigating acupuncture’s neural mechanisms in real clinical settings. This non-invasive technique tracks cortical hemodynamic responses by detecting oxygenated and deoxygenated hemoglobin concentrations based on the neurovascular coupling principle. Compared to functional magnetic resonance imaging (fMRI), fNIRS is portable, resistant to motion artifacts, and cost-effective. It also allows patients to receive acupuncture in a natural sitting posture, making it particularly suitable for real-time monitoring in real-world clinical settings (Xu et al., 2025). Compared with electroencephalography (EEG), fNIRS provides better signal stability and spatial accuracy (Wang et al., 2020). Furthermore, fNIRS has been successfully employed to investigate individual central responses to acupuncture in natural clinical environments (Cao et al., 2026; Qu et al., 2026).

Accordingly, this randomized controlled trial aims to elucidate the central mechanism of acupuncture for UP by using fNIRS to assess brain responses to immediate and long-term acupuncture interventions. We hypothesize that, compared to sham acupuncture (SA) and waiting-list (WT) controls, verum acupuncture (VA) will specifically regulate neural activity patterns in the prefrontal cortex (PFC) and primary somatosensory cortex (S1) in response to itch. We further hypothesize that these neural changes will correlate with clinical symptom improvement. Therefore, this study aims to elucidate the central mechanism of acupuncture for UP, thereby providing insights into the scientific basis of acupuncture for UP and supporting its precise clinical application.

## Methods and analysis

2

### Study design

2.1

This is a randomized clinical trial based on fNIRS, and a total of 96 patients with UP will be enrolled. Patients will be randomly divided into three groups (VA, SA, or WT groups) in a ratio of 1:1:1 after meeting the inclusion criteria. Participants in the VA and SA groups will receive one session of immediate verum or sham acupuncture during scanning, followed by 4 weeks of long-term verum or sham acupuncture treatment, respectively. The clinical evaluation and fNIRS scans are presented in Figure 1 and Table 1. The study is following the Standard Protocol Project Items: Recommendations for Intervention Trials (SPIRIT) guidelines, the principles of Consolidated Standards of Reporting Trials (CONSORT), and the Standards for Reporting Interventions in Clinical Trials of Acupuncture (STRICTA).

**Figure 1 fig1:**
[figure not shown]
Flow chart of the trial. VA, verum acupuncture; SA, sham acupuncture; WT, waiting-list; fNIRS, functional near-infrared spectroscopy.

**Table 1 tab1:** Schedule of enrollment, interventions, fNIRS scan, and assessment.

Time point	Study period					
	Baseline		Treatment phase			
	1-week	0-week	1-week	2-week	3-week	4-week
Enrollment						
Eligibility screen	×					
Informed consent	×					
Randomization		×				
Interventions						
VA group			×	×	×	×
SA group			×	×	×	×
WT group						
fNIRS Scan						
VA group		×^ ***** ^		×		×
SA group		×^ ***** ^		×		×
WT group		×^ ***** ^		×		×
Assessment						
VAS of cowhage induced itch			×			
24 h-WI-NRS		×	×	×	×	×
UP-dial		×				×
PHQ-9		×				×
GAD-7		×				×
Adverse events		×	×	×	×	×
Blinding						×^ **#** ^

*means the first fNIRS scan will be performed for both measuring the immediate antipruritic effect of acupuncture induced by the cowhage test and the long-term effects before the 4-weeks treatment. #means after completing the 4-week trial and final clinical evaluation, participants in the VA and SA groups will be asked to guess whether they received verum acupuncture, sham acupuncture, or were unaware of it. VA, verum acupuncture; SA, sham acupuncture; WT, waiting-list; fNIRS, functional near-infrared spectroscopy; VAS, visual analogue scale; 24 h-WI-NRS, 24-h Worst Itch Numeric Rating Scale; UP-Dial, Uremic Pruritus in Dialysis patients; PHQ-9, Patient Health Questionnaire-9; GAD-7, Generalized Anxiety Disorder Scale-7.

### Ethics

2.2

This study has been approved by the Institutional Review Board and Ethics Committee of Chengdu Pidu District Traditional Chinese Medicine Hospital (No. K-2025-011) and registered on September 26, 2025, in the International Traditional Medicine Clinical Trial Registry of World Health Organization, an international clinical trial registration platform (ITMCTR2025001844).

### Recruitment

2.3

This study will be carried out from March 2026 to December 2027 at Chengdu Pidu District Traditional Chinese Medicine Hospital. UP patients will be recruited from the blood purification center of this hospital.

### Participants

2.4

#### Diagnostic criteria

2.4.1

UP is diagnosed according to the ESRD criteria, characterized by itching that cannot be attributed to other causes (Fishbane et al., 2020a, 2020b). Based on the KDIGO 2024 Clinical Practice Guidelines for the Evaluation and Management of chronic kidney disease, patients with eGFR<15[ml·min^−1^(1.73 m^2^)^−1^ sustained for ≥ 3 months meet the diagnostic criteria for ESRD (Kidney Disease: Improving Global Outcomes (KDIGO) CKD Work Group, 2024).

#### Inclusion criteria

2.4.2

Patients who match all the following items will be included:1) Meet the diagnostic criteria for UP and lasts for 6 weeks or longer, and 2) moderate to severe itch of UP (average weekly score of 24-h Worst Itch Numeric Rating Scale (24 h WI-NRS) in the past week≥ 4 points), and 3) aged 18 to 65 years with right-handed, and 4) have been regularly undergoing hemodialysis for more than 3 months, and 5) within the first 3 months before enrollment, at least one single chamber urea clearance rate (spKt/V) of ≥ 1.2 and urea decline rate (URR) of ≥ 65%, and 6) not combined with serious mental illness or cognitive impairment, and 7) not combined with neurological diseases such as cerebral hemorrhage and cerebral infarction, and 8) without alcohol or drug addiction, 9) medications for UP, such as antihistamines, gabapentin, topical emollients, and other antipruritic agents, need to maintain a stable dosage for at least 1 month before enrollment, and any newly increased antipruritic drugs are forbidden during the trial, and 10) not participating in other clinical trials currently, and 11) sign informed consent before conducting the trial.

#### Exclusion criteria

2.4.3

Patients will be excluded if they:1) have other skin diseases that can cause itching, such as psoriasis, atopic dermatitis, urticaria, contact dermatitis, etc., and 2) suffer from any severe chronic liver disease, or any one of alanine aminotransferase, aspartate aminotransferase, glutamyltransferase, or total bilirubin exceeding twice the upper limit of normal values, and 3) with malignant tumors or other serious illnesses that require hospitalization, and 4) with severe mental illness or cognitive impairment (such as dementia), and 5) only experience itching during hemodialysis, and 6) have undergone physical therapy such as acupuncture or moxibustion within 1 month to address itching symptoms, and 7) present with coagulation dysfunction or local skin infection and ulceration, and 8) pregnant or lactating women.

### Sample size

2.5

Since this trial will take the therapeutic effects of acupuncture on UP as the foundation and further explore its central mechanism via fNIRS, 24 h-WI-NRS will be used as the primary clinical outcome for this sample size calculation (Fishbane et al., 2020a, 2020b), with VA versus SA defined as the primary comparison; meanwhile, the WT group will serve as an auxiliary control to separate spontaneous disease fluctuation. Based on our preliminary pilot trial, the 24 h-WI-NRS mean differences were 3.68 ± 1.30 for the VA group and 1.64 ± 2.55 for the SA group after 4-week interventions compared to baseline. Using G*Power software with two-tailed tests, effect size = 1.01, *α* = 0.05, and 1-*β* = 0.95, this study requires 27 patients per group. Accounting for a 15% dropout rate, each group should enroll 32 patients; a total of 96 patients will be included across three groups.

### Randomization

2.6

To avoid selection bias, the randomization will be performed with a computer-generated randomization digital table to assign these 96 patients into VA, SA, and WT groups in a 1:1:1 ratio. The sealed envelopes will be used to inform the acupuncturist what kind of acupuncture the patient will receive.

### Blinding

2.7

Since the acupuncturist is always aware of the grouping of patients, the acupuncture manipulation will be concealed from participants, researchers, outcome evaluators, and statisticians. Researchers, the acupuncturist, outcome evaluators, and statisticians are separate. To minimize non-specific effects arising from acupuncturist-participant interaction, a standardized communication script will be implemented across all groups, restricting conversation to neutral, pre-specified phrases (e.g., greeting, procedural instructions, and safety checks only). To assess blinding success, after completion of the 4-week trial and final clinical assessment, participants in the VA and SA groups will be asked to guess whether they received verum acupuncture, sham acupuncture, or were unaware of it; the Bang blinding index will then be calculated for these two groups.

### Cowhage test for inducing pruritus

2.8

The primary neuronal transmission pathway of UP is mediated by non-histamine pathways. Hence, the cowhage test could induce acute pruritus in UP patients (Papoiu et al., 2014). According to previous studies (Zuo et al., 2023), about 20 cowhage spicules will be applied using a gloved finger to a 2 cm diameter area located about 5 cm below the elbow of the patient’s non-fistula forearm. The spicules will then be gently rubbed on the skin in a circular motion for 30 s. The itch-inducing procedure will take approximately one minute. Pruritus intensity will be assessed every minute for 5 min using a 0–10 visual analogue scale (VAS). After the test, spicules will be completely removed using adhesive tape.

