### Core neuroimaging indicator: fNIRS data acquisition

2.11

Based on the efficacy of acupuncture for UP, this study will further focus on its central mechanism. According to previous studies (Mochizuki and Kakigi, 2015; Sun, 2025), we hypothesize that acupuncture’s antipruritic effect of UP correlates with modulation of cortical regions involved in itch processing, particularly the prefrontal cortex (PFC) and primary somatosensory cortex (S1), which can be captured in real-time by portable fNIRS. Moreover, considering that the oxyhemoglobin (HbO) signal has a better signal-to-noise ratio and is more reliable and sensitive than the deoxyhemoglobin signal (Strangman et al., 2002; Dravida et al., 2018), this trial will use cortical HbO changes to characterize the functional activity of PFC and S1, two regions of interest (ROIs). Therefore, the HbO change of task-state scanning data during the first fNIRS scan will be the primary outcome of the immediate effect of acupuncture on relieving itch, and the resting-state scanning data after 0−/2−/4-week interventions will be the primary mechanistic outcome of acupuncture’s long-term effect on UP.

Patients will undergo three fNIRS recording sessions. Each fNIRS scan will be scheduled on non-dialysis days or before dialysis sessions to minimize the influence of acute biochemical fluctuations. The first fNIRS scan will be conducted before the long-term acupuncture treatment, including an 8 min rest scanning and a 5 min task scanning during acupuncture treatment with immediate itch induction by the cowhage test (Figure 2A). Another two fNIRS scans will be performed after the 6th and 12th long-term acupuncture treatments, with only the 8 min rest scanning.

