**Figure 2 fig2:**
[figure not shown]
fNIRS data acquisition. **(A)** fNIRS scanning process diagram; **(B)** fNIRS channels location.

A portable fNIRS instrument (LIGHTNIRS, Shimadzu Corporation, Japan) will be utilized to measure cortical hemodynamic response, with a sampling rate of 13.33 Hz at wavelengths 780 nm and 830 nm. Due to PFC and S1 being ROIs of the mechanism hypothesis in this study, the optodes of fNIRS will be positioned over the prefrontal and bilateral primary somatosensory cortex. The fNIRS cap is created by 8 × 2 light sources and detectors (20 channels) placed according to the international 10–20 EEG system, with a separation distance of 2.5–3 cm for all optodes (Figure 2B). To achieve precise spatial registration, the Montreal Neurological Institute coordinates of all optodes will be measured using an electromagnetic 3D digitizer system, and the corresponding brain regions of the midpoint of each channel in the Brodmann Talairach template will be calculated.

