#### fNIRS data analysis

2.14.2

The fNIRS data will be processed and analyzed using the MATLAB 2020b software.

In lines with prior fNIRS studies investigating acupuncture (Qu et al., 2022; Si et al., 2021), fNIRS data preprocessing will be implemented using the Homer2 toolbox, which mainly including: (1) noisy channels will be rejected if any of the following criteria are met: the optical intensity (OI) falls outside the range of 0.5–1,000, the source-detector separation deviates over the range from the 0–45 mm (Broscheid et al., 2022), or the ratio between the mean optical intensity and its standard deviation [mean(OI)/std.(OI)] is less than 2; (2) at the participant level, if over 50% of a participant’s total channels are flagged as noisy, the entire dataset of this participant will be discarded due to insufficient signal quality; (3) the raw NIRS light intensity will be converted to an optical density (OD) signal; (4) the function hmrMotionArtifactByChannel will be used to identify motion artifacts; (5) then the motion correction will be conducted with the spline interpolation algorithm implemented in the function hmrMotioncorrectionSpline; (6) the interference of physiological noises will be reduced using a 0.01–0.2 Hz bandpass filter; and (7) the filtered OD data will be converted into the concentrations of HbO based on the modified Beer–Lambert law. Then, the hemodynamic response function will be estimated by a general linear model approach that uses ordinary least squares to get an average response for each of 20 CHs in every participant. Brain activation analysis will be conducted, and based on Montreal Neurological Institute (MNI) coordinates, CHs covering PFC and S1 will be predefined as the ROIs for subsequent functional connectivity analysis.

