Given that the first fNIRS session includes both resting-state and task-state (cowhage-induced itch with VA or SA intervention, or WT control) scanning, while the 2−/4-Week-4 sessions only include resting-state scanning, these data will be analyzed separately according to different physiological states. Specifically, for the immediate effect of acupuncture antipruritus, the task-induced hemodynamic change (ΔHbO = task-state minus resting-state) during the first fNIRS scan will be calculated for each group. Since this is a single time-point measurement, the comparison (VA vs. SA vs. WT) of theseΔHbO values will be performed using one-way ANOVA. For the long-term effect of acupuncture antipruritus, only resting-state fNIRS data will be acquired at three time points (0−/2−/4-week). To account for the repeated-measures design across the three time points, LMM will be applied to longitudinal hemodynamic responses, with time, group, and their interaction as fixed effects, and a random intercept for each participant. The resting-state outcome measures will comprise: (1) regional HbO activity, defined as the temporal mean of the HbO concentration over the resting-state period for each channel; and (2) HbO-based functional connectivity, calculated as Fisher’s Z-transformed Pearson correlation coefficients between the time series of all channel pairs within and across the PFC and S1. The significance threshold is set to *p* < 0.05, and FDR correction will be strictly applied to control for multiple comparisons.

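### The cowhage side follows each patient's fistula, but the task-scan S1 response is not aligned to it, so the S1 contrast is diluted to an unknown degree

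*Protocol article*

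**What the plan says.** Section 2.8 sets the stimulation site by vascular access: spicules are applied to an area "located about 5 cm below the elbow of the patient’s non-fistula forearm". The only laterality criterion is handedness: section 2.4.2 admits patients "aged 18 to 65 years with right-handed" and says nothing about fistula side. Section 2.6 describes 1:1:1 randomization and names no stratification factor.

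For the recording, section 2.11 states that "the optodes of fNIRS will be positioned over the prefrontal and bilateral primary somatosensory cortex". Section 2.14.2 fits a general linear model "to get an average response for each of 20 CHs in every participant", and then, on the basis of MNI coordinates, "CHs covering PFC and S1 will be predefined as the ROIs for subsequent functional connectivity analysis". Channels are thus identified by where they sit on the head, not by their side relative to the itch.

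The outcome affected matters: by section 2.11, "the HbO change of task-state scanning data during the first fNIRS scan will be the primary outcome of the immediate effect of acupuncture". Section 2.14.2 forms this outcome as task minus rest at the first scan and compares the verum (VA), sham (SA) and waiting-list (WT) arms by one-way ANOVA. No side term is mentioned, and no step relabels or mirrors channels.

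**The concern.** A stimulus on one forearm is expected to drive S1 mainly, though not necessarily only, in the opposite hemisphere. If the stimulated arm varies, the same left S1 channel records the mainly responding side in one patient and the other side in the next. The arm mean for that channel is then a mixture of two different quantities.

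This has two consequences. The VA–SA contrast at an S1 channel shrinks towards the average of the contralateral and ipsilateral effects, and patients within an arm differ more than they need to. S1 is one of only two regions that the mechanistic hypothesis names, so the risk is a missed S1 effect in the primary outcome for the immediate effect of acupuncture.

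**Working it through.** **Plan's own figure.** The sample size rests on the itch score (24 h-WI-NRS), not on fNIRS, but it supplies the number per arm. From section 2.5, the changes are 3.68 ± 1.30 (VA) and 1.64 ± 2.55 (SA).
- Pooled SD = √((1.30² + 2.55²)/2) = 2.024, so d = 2.04/2.024 = 1.008, in line with the stated 1.01.
- A two-sided two-sample t-test at α = 0.05 and power 0.95 needs 26.48, rounded up to 27 per arm (power 0.954).
- 27/0.85 = 31.8, rounded up to 32, and 3 × 32 = 96.

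The figure reproduces, and this point does not change it.

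**Inputs for the dilution.** From the protocol: 27 evaluable patients per arm and two-sided α = 0.05. Assumed, because the protocol gives no value:
- p, the share of patients stimulated on the less common side: 0.1 to 0.4.
- r, the ipsilateral response and VA–SA effect as a fraction of the contralateral ones: 0, 0.5, 0.8 or 1.
- A VA–SA contrast of d = 0.8 when channels are aligned.
- A mean contralateral response of about 1 SD, which sets the added variance.

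**Formulas.** Take an S1 channel that is contralateral in most patients.
- Contrast multiplier: m = (1 − p) + p·r
- Variance relative to aligned data: v = 1 + p(1 − p)(1 − r)²
- Diluted effect: d′ = 0.8·m/√v

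Example with p = 0.4 and r = 0.5: m = 0.6 + 0.2 = 0.80; v = 1 + 0.24 × 0.25 = 1.06; d′ = 0.64/1.030 = 0.62; power 61%.

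**Results** (two-sample t-test, 27 per arm; 82% power when aligned):

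| r | d′ at p = 0.1 | Power | d′ at p = 0.4 | Power |
|---|---|---|---|---|
| 1 (fully bilateral) | 0.80 | 82% | 0.80 | 82% |
| 0.8 | 0.78 | 81% | 0.73 | 75% |
| 0.5 | 0.75 | 77% | 0.62 | 61% |
| 0 (strictly contralateral) | 0.69 | 70% | 0.43 | 34% |

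With p = 0 (all fistulas on one side) there is no loss for any r. At the mirror-image channel, which is contralateral only in the minority, m = p + (1 − p)·r. When r is below 1 and p below 0.5 this is smaller still.

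These are powers for a single pairwise VA–SA comparison with no multiplicity correction. They show the relative loss and are not forecasts for the planned three-arm ANOVA.

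**Chance imbalance.** The difference in stimulated-side share between two arms of 32 has SD √(2p(1 − p)/32). This is 7.5 percentage points at p = 0.1 and 12.5 points at an even split.

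**The case against.** **Unit of the group test.** The per-channel wording belongs to the within-patient model, which any remedy also needs. The sentence on the ANOVA does not say whether it is run by channel or by region, and section 2.11 speaks of two regions of interest. A condensed article may also leave relabelling to a fuller document. This is fair as to certainty, but no reading of the text removes the problem. If left and right S1 are pooled into one region, the side mix cancels, yet contralateral and ipsilateral signals are averaged within each patient, giving a contrast multiplier of (1 + r)/2, or 0.75 at r = 0.5. The article does fix the channel definition, the outcome and the test, and none of them refers to the stimulated side.

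**Strict lateralisation.** This objection stands. VA and SA both receive cowhage and differ only in the needling, which is at bilateral points (2.9), with needles retained during the task scan (2.9.1). A VA–SA difference confined to one hemisphere is therefore the extreme case. A reader might take the 70–34% row as the expected loss; the documents do not support that.

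**Bias.** A reader might also infer that an uneven side mix between arms biases the comparison. It does not. Fistula side does not depend on allocation, so it is balanced in expectation, and chance imbalance is ordinary sampling variation that the ANOVA error covers.

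**Multiplicity.** It is tempting to add that FDR over up to 190 channel pairs (20 × 19/2) weakens the analysis further. Those pairs, "between the time series of all channel pairs within and across the PFC and S1", are a resting-state measure that the cowhage side does not affect, and channelwise FDR against regional averaging is a design preference. That argument does not belong here.

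**Conclusion.** The point holds as a loss of precision in one analysis. As written, the plan can mix contralateral and ipsilateral S1 responses in the primary immediate-effect outcome, with no alignment or adjustment. The effect is dilution and added variance, not systematic bias.

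The size cannot be fixed from the documents. Under the assumptions above it runs from about one percentage point of power (82% to 81%) to a fall to 61% with a half-size ipsilateral effect. The fall to 34% needs both a 40% side mix and no ipsilateral effect at all. There is no loss if every fistula is on the same side or the response is fully bilateral, but the protocol states neither.

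The scope is narrow: the S1 part of the task scan and any correlation that uses it. The 24 h-WI-NRS, the cowhage VAS, the PFC as a single region, the resting-state analyses and the sample size do not depend on this point.

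**What to change.** Record for every patient which forearm received the cowhage. Before the group analysis of the task scan, relabel S1 channels as contralateral or ipsilateral to that forearm, and include stimulated side as a covariate in the ΔHbO comparison across the three arms. State this in the protocol or analysis plan before any task data are examined, because a labelling chosen afterwards would be open to the charge of being data-driven.

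The arm used for stimulation, the sample size (27 evaluable, 32 enrolled per arm, 96 in total) and the resting-state analyses stay as they are. The cost is one recorded item and a little extra code. Relabelling also assumes that the left and right S1 channels are homologous; the digitised optode positions planned in section 2.11 allow that to be checked.
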